## Methods/Design

### Study design

To formally validate whether *APOE isoform*, which is formed by *rs7412* and *rs429358,* and *CYP7A1 rs3808607* can predict responsiveness to PS consumption across the general population, the present proposal is to carry out a double-blind, placebo-controlled, randomized two-period crossover study to investigate the LDL-C responsiveness to the controlled administration of PS. The PS treatment will consist of two daily single portions of margarine, providing 1 g each of PS during the PS period (2.0 g/day of PS in total). The placebo treatment will be an identical margarine, except it will not contain any added PS. Both the PS and placebo margarine treatments will be coded by the industrial partner organization, Unilever, and provided to the research group to maintain blinding of both the researchers and participants throughout the clinical trial.

We have two original specific hypotheses. 1) *APOE isoform* and *CYP7A1 rs3808607* will independently predict the response to PS consumption in a pattern that reflects the current gene-biomarker associations as outlined in Table 1. *APOE ε4/−* will be more responsive to PS than *ε3/ε3*. The *CYP7A1 rs3808607* G allele will predict responsiveness to PS consumption in a dose-responsive fashion, with T/T predicting nonresponse. 2) The genosets formed by combinations of *APOE isoform* and *CYP7A1 rs3808607* will follow the pattern as predicted in Table 2.

**Table 2 Tab2:** Original plant sterol trial genotype recruitment targets and predicted response

ApoE	CYP7A1	Predicted response	Planned recruitment
ε2/−	T/T	Nonresponder	*n* = 8
ε2/−	G/−	Responder	*n* = 8
ε3/ε3	T/T	Non-responder	*n* = 8
ε3/ε3	T/G	Responder	*n* = 8
ε3/ε3	G/G	Responder	*n* = 8
ε4/−	T/T	Responder	*n* = 8
ε4/−	T/G	Responder	*n* = 8
ε4/−	G/G	Responder	*n* = 8

Because of the amount of time spent on recruitment and the difficulty in finding participants who were eligible with rare combinations of genosets, the APOE 2 groups were removed, and other groups were combined. To maintain the study power, we increased the *n* in the other groups as described in Table 3.

**Table 3 Tab3:** Amended plant sterol trial genotype recruitment targets and predicted response

ApoE	CYP7A1	Predicted response	Planned recruitment
ε3/ε3	T/T	Nonresponder	*n* = **20**
ε3/ε3	G/−	Responder	*n* = 22
ε4/−	−/−	Responder	*n* = 22

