The trial will use a priori recruitment of 64 individuals (Table 3) with the specific SNPs associated with responsiveness to PS at a) the University of Manitoba’s Richardson Centre for Functional Foods and Nutraceuticals (RCFFN) and b) Seven Oaks General Hospital (SOGH) in Winnipeg, Manitoba, Canada. The present trial will therefore select individuals from the general population with specific SNPs and then test their responsiveness to PS consumption. These responsiveness characterizations will generate the required data to validate the genoset-based classifications of responders and nonresponders.

Each treatment period will consist of 28 days, with a minimum washout of 21 days between periods. Figure 1 shows the schematic flow diagram of the trial protocol.

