### Randomization

Eligible participants will be randomly allocated to two groups: the PS treatment group or the placebo group for the first period, and then, participants will switch treatments for the second period after the washout between periods. Randomization will be done by an assistant outside of the research team using a block randomization method through sealed envelopes with stratification by sex and genoset. Randomization in blocks of eight and four, each with equal numbers of treatment orders will be used. This blocking is being done to minimize imbalances in treatment orders within each genoset group or by sex. Administration of the intervention will be conducted in a double-blind manner. Single portion tubs of PS treatment and placebo margarine are being created for this study by Unilever and are being delivered to the research team in identical packages labeled either A or B.

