## Sample size calculation and statistical analysis

The sample size, with a minimum of 20 participants for each individual genotype and *n* = 20–22 for each individual genoset, is based on previous work performed by this research group [13]. A power calculation was performed using PROC POWER SAS Institute (version 9.4) using the paired means statement to model the AB/BA crossover design (corr = 0.75, a = 0.05 and b = 0.80); based on an average reduction in LDL-C of 0.34 mmol/L resulting from PS consumption according to the meta-analysis findings of Demonty et al. [8], the standard deviations in LDL-C for placebo (0.67 mmol/L) and PS (0.7 mmol/L) from the MacKay et al. [11] and a correlation in LDL-C values of 0.75, which was an estimate based on variability in LDL-C concentrations over time from MacKay et al. [11] and on a within-persons correlation in cholesterol response to plant sterols [15]. From this power calculation, we determined that 18 participants would be needed for each genoset to detect a response, in the form of a significant reduction in LDL-C from placebo to plant sterol consumption period, in the group. Our objective was to test if each genoset would respond, with the hypothesis that the *CYP7A1 rs3808607T/T* and *APOE E3/3* genoset would not respond to plant sterol consumption with LDL-C lowering.

Given the crossover design, the study outcomes measures will be analyzed in a per-protocol population where only participants who received both treatment and placebo are included. The effects of treatment, comparing the endpoint values of the treatment and placebo periods, will be analyzed by the SAS MIXED procedure. Sequence and sex will be included in the model as fixed factors, while participants will be included as a random and repeated factor. Genoset and treatment by genoset will be included as fixed factors to assess the impact of the genoset on the treatment. The impact of the individual genotypes will also be investigated individually. Significant treatment-by-genoset or treatment-by-genotype effects will be examined by the SAS SLICE function, with Bonferroni correction for the number of slices. Treatment effect sizes by genoset or genotype, from significant interactions, will be compared by t test or ANOVA using the difference in mixed-model least squares means summary statistics for the treatment effect slices, with Tukey-Kramer adjustment for multiple comparisons [13].

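### The stated crossover model has no period effect, so a common period shift would make the genoset tests conservative and, where treatment orders are unbalanced, bias genoset effects modestly

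*Protocol article*

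**What the plan says.** The statistical section of the protocol article states that treatment effects, "comparing the endpoint values of the treatment and placebo periods, will be analyzed by the SAS MIXED procedure". It then lists the terms: "Sequence and sex will be included in the model as fixed factors, while participants will be included as a random and repeated factor", and "Genoset and treatment by genoset will be included as fixed factors to assess the impact of the genoset on the treatment". No period or visit term appears there or elsewhere in the article. Because endpoint values are compared, the period baselines do not enter the stated model.

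On design, the article says: "Each treatment period will consist of 28 days, with a minimum washout of 21 days between periods". Treatment order is randomised in blocks of eight and four, stratified by sex and genoset, and the stated purpose is: "This blocking is being done to minimize imbalances in treatment orders within each genoset group or by sex". During the trial the recruitment groups changed: "the APOE 2 groups were removed, and other groups were combined". The analysis is restricted to participants who received both treatments. Under Discussion, genosets that do not show a significant LDL-C reduction are to be called nonresponders.

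**The concern.** The two endpoint measurements are at least 21 + 28 = 49 days apart. Any change common to participants over that time, such as adaptation to the study routine or drift in diet, shifts period 2 against period 1. In an AB/BA design this shift is a within-participant quantity, and it appears as an interaction between treatment and sequence. The sequence main effect is a between-participant term and cannot absorb it, nor can the participant effect. Naming participant as a repeated factor describes the covariance and estimates no period mean.

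The consequence bears on the trial's main claim. The central hypothesis is that ε3/ε3 with T/T does not respond, and the label rests on non-significance. A model that carries avoidable residual error makes non-significance more likely in every genoset. Where the orders are unbalanced within a genoset, part of the shift also enters its estimated effect.

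**Working it through.** **Inputs from the article.** Effect 0.34 mmol/L ("based on an average reduction in LDL-C of 0.34 mmol/L resulting from PS consumption"); SDs 0.67 (placebo) and 0.70 (plant sterol); "corr = 0.75, a = 0.05 and b = 0.80", with b read as power and α taken as two-sided; planned genosets of 20, 22 and 22.

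**Assumptions.** Period shift π of 0.1, 0.2 or 0.3 mmol/L (none is given); three Bonferroni slices; all 64 participants complete.

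**The plan's own figure.** Variance of the paired difference = 0.67² + 0.70² − 2 × 0.75 × 0.67 × 0.70 = 0.2354, so the SD is 0.485. A paired t test (noncentral t) has power 0.800 at n = 18 and 0.774 at n = 17. The stated 18 per genoset reproduces.

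**Effect of omitting period.** Let δ be the true plant sterol minus placebo effect and π the shift in period 2. A participant's difference has mean δ − π if plant sterol comes first and δ + π if it comes second. For a genoset of size n:

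- bias = π × (number with plant sterol second − number with it first)/n
- variance of the difference with equal numbers = 0.2354 + π²

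**Balanced orders.** The within-participant degrees of freedom are 64 − 3 = 61. Slice power at n = 22, δ = 0.34 in absolute value, α = 0.05/3:

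| π (mmol/L) | SD of difference | Variance increase | Power |
|---|---|---|---|
| 0 | 0.485 | none | 0.79 |
| 0.1 | 0.495 | 4% | 0.77 |
| 0.2 | 0.525 | 17% | 0.72 |
| 0.3 | 0.570 | 38% | 0.63 |

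With period in the model (60 df), power stays at 0.79 whatever π is. In simulation of the three-genoset model with balanced orders and π = 0.2, the estimates were unbiased. Type I error at nominal 0.05 fell to 0.033, and power of the treatment-by-genoset test fell from about 0.61 to 0.53. The article examines slices only after a significant interaction, so that loss comes first.

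**Unbalanced orders, n = 20.**

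| Split | π = 0.1 | π = 0.2 |
|---|---|---|
| 11:9 | 0.01 | 0.02 |
| 12:8 | 0.02 | 0.04 |

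The SE of a genoset effect is 0.485/√20 = 0.108, so 0.04 is 0.37 of an SE and 12% of 0.34. A random-intercept model fitted to simulated data (12:8, π = 0.2, true effect 0) gave −0.044 with sequence and sex only, and −0.003 once period was added. Residual variance fell from 0.139 to 0.118.

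**How often imbalance arises.** This was simulated for a genoset of 20 split over two sex strata, with blocks of four and eight mixed at random (assumed). An imbalance of 2 or more occurs in about half of trials and of 4 or more in about 5%, or 7–8% with 10% dropout. A split of 13:7 or worse occurs in about 0.1% without dropout.

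The ε3/ε3 T/T genoset is a single cell in both Table 2 and Table 3, so these figures apply to it. ε3/ε3 G/− was formed from two former cells and ε4/− from three. If all their members had been randomised within the old cells, an imbalance of 4 or more would occur in roughly 16–29% of trials. The article does not say how many were. In the single-genotype analyses, CYP7A1 genotype is not a stratum within the amended ε4/− group, so order is not balanced by design there.

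**The case against.** The strongest reply is that the article condenses a fuller protocol and its term list is loose: treatment itself is only implied as a factor. Period may be in the actual program. That is possible, but the text names sequence and sex and omits the one nuisance term that acts on the within-participant contrast, so the model as stated needs correcting.

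The second reply is that π is unknown and may be small. This stands. At π = 0.1 the loss is two points of power. Values of 0.2 and 0.3 are 59% and 88% of the assumed treatment effect and should be read as a stress range. Participants are also asked to keep their usual diet and activity, with weekly checks.

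Some stronger readings are tempting, and the document does not support them:

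- **False positives are inflated.** With balanced orders the reverse holds: the test is conservative. It is the residual error that grows.
- **Genoset effects are seriously biased.** Stratified blocking makes large splits uncommon, and over repeated randomisation the bias averages to zero. It is conditional on the imbalance that occurs.
- **The mid-trial merger upset the key genoset.** ε3/ε3 T/T was not merged.
- **Season or regression to the mean must produce a shift.** Recruitment has been rolling since July 2016, so period 2 falls in different seasons for different people. Both endpoints follow screening, so they regress largely alike.
- **Power falls below 0.60 at π = 0.3.** At n = 22 that requires each genoset to be tested on its own degrees of freedom. Slices from the mixed model use the pooled error, which gives 0.63.

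**Conclusion.** The point holds for the model as the article states it: without a period term, a common period shift is left in the residual and, under imbalance, in the genoset effects. The main harm is lost power in a trial that reads non-significance as nonresponse: about 2, 7 or 16 percentage points per responder genoset of 22 at π of 0.1, 0.2 or 0.3 mmol/L. The bias is secondary: 0.02 to 0.04 mmol/L at π = 0.2 for splits of 11:9 to 12:8, with more exposure in the merged genosets and the CYP7A1 single-genotype analyses. All sizes depend on an assumed π and on the article's planning SDs and correlation. This should be fixed, but it does not invalidate the design.

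**What to change.** Add period (1 or 2) as a fixed effect in the MIXED model for LDL-C and the secondary outcomes, including the single-genotype analyses. Keep treatment, sequence, sex, genoset, treatment-by-genoset and the participant effect as stated. Record the change before unblinding.

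The cost is one within-participant degree of freedom, from 61 to 60. Slice power at n = 22 with no period shift goes from 0.793 to 0.792. Even for a single genoset of 18 tested alone at α = 0.05, it goes only from 0.800 to 0.797. No new data or participants are needed.

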Therefore, the primary specific hypothesis of this study after these protocol amendments are 1) the genoset formed from *CYP7A1 rs3808607T/T* and *APOE E3/3* predict nonresponse*,* and 2) *APOE isoform ε4/−* and *CYP7A1 rs3808607 G/−* will independently predict response to PS consumption in a pattern that reflects the current gene-biomarker associations outlined in Table 1. For these hypotheses, response is being defined as a reduction in the LDL-C concentrations due to plant sterol consumption.

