
#### Inclusion criteria

Men and women aged 18–70 years and with LDL-C concentrations of 3.0–4.9 mmol/L will be recruited into the trial. Participants must have a fasting glucose concentration of < 6.1 mmol/L. A prospective recruitment scheme based on genotype will recruit 20–22 individuals in each of the three most common combinations, also called genosets, (outlined in Table 3). This approach would leave a minimum sample size of 20 participants for each individual genotype. The prospective recruitment based on genosets of interest will require screening of 200–400 potential participants. Such lengthy screening is required to find sufficient individuals who have the rarer genosets and meet all the inclusion and exclusion criteria. Additionally, participants must be willing to fast for 10–12 h before blood sampling, abstain from alcohol for 2 days prior to blood sampling, and abstain from coffee and physical exercise for at least 12 h before measurements and blood sampling. All participants must be able and willing to give informed consent to participate in the trial prior to their inclusion.

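### The single-gene analyses do not separate APOE from CYP7A1 in this quota sample, so the independent-prediction hypothesis needs a model with both genes and within-stratum contrasts

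*Protocol article*

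**What the plan says.** The second amended hypothesis (Protocol article, Background) is that ε4/− and G/− "will independently predict response to PS consumption in a pattern that reflects the current gene-biomarker associations outlined in Table 1".

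Study design reports that recruitment difficulty led to an amendment: "the APOE 2 groups were removed, and other groups were combined". Table 3 then sets three quotas: ε3/ε3 T/T (20, predicted not to respond), ε3/ε3 G/− (22, predicted to respond) and ε4/− with any CYP7A1 genotype (22, predicted to respond).

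The section on sample size and analysis fits a mixed model with treatment, a three-level genoset factor and their interaction. It adds: "The impact of the individual genotypes will also be investigated individually". After a significant interaction, treatment effects are compared between genosets or genotypes with Tukey-Kramer adjustment. No model with APOE and CYP7A1 together is stated.

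Inclusion criteria adds: "This approach would leave a minimum sample size of 20 participants for each individual genotype".

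**The concern.** A claim that each gene predicts response independently has to hold the other gene constant. In the pre-amendment targets (Table 2), T/T made up 8 of 24 in ε3/ε3 and 8 of 24 in ε4/−, so CYP7A1 was balanced between those two APOE groups. The amendment removed that balance. The T/T share is now set by quota in ε3/ε3 and by whoever is recruited in ε4/−.

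Pooling over the other gene can therefore credit APOE with a CYP7A1 effect, or the reverse. The Discussion foresees advising people according to their genetic class, so crediting the wrong gene would matter.

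**Working it through.** **Inputs from the article.** Correlation, alpha and power: "corr = 0.75, a = 0.05 and b = 0.80" (the last is read as power). Effect: "based on an average reduction in LDL-C of 0.34 mmol/L resulting from PS consumption". Spread: "the standard deviations in LDL-C for placebo (0.67 mmol/L) and PS (0.7 mmol/L". Quotas: 20, 22 and 22.

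**Assumed.** k is the number of T/T among the 22 ε4 carriers, which the article does not give; f = k/22.

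**The plan's own figure.** SD of the paired difference = √(0.67² + 0.70² − 2×0.75×0.67×0.70) = 0.485. The smallest n giving 80% power in a two-sided 5% paired t test for 0.34 is 18 (power 0.800). This agrees with the article: "we determined that 18 participants would be needed for each genoset to detect a response". The present point does not affect that figure.

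**Quota share.** T/T in ε3/ε3 = 20/42 = 47.6%.

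**False APOE contrast if only CYP7A1 matters** (T/T responds 0, G/− responds 0.34): 0.34×(1 − f) − 0.34×22/42 = 0.34×(20/42 − f).

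**False CYP7A1 contrast if only APOE matters** (ε4/− responds 0.34 more): 0.34×[(22 − k)/(44 − k) − k/(20 + k)].

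| T/T in ε4/− | False APOE contrast | False CYP7A1 contrast | Type I error, single-gene model |
|---|---|---|---|
| 4/22 | 0.34×(0.476 − 0.182) = 0.100 | 0.34×(0.450 − 0.167) = 0.096 | about 10% |
| 6/22 | 0.34×(0.476 − 0.273) = 0.069 | 0.34×(0.421 − 0.231) = 0.065 | about 6.5% |
| 8/22 | 0.34×(0.476 − 0.364) = 0.038 | 0.34×(0.389 − 0.286) = 0.035 | about 5% |
| 10/22 | 0.34×(0.476 − 0.455) = 0.007 | 0.34×(0.353 − 0.333) = 0.007 | no inflation |

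The error rates come from simulating each person's treatment difference (SD 0.485, N = 64). A calculation that keeps the residual SD at 0.485 gives 12%, 8.3% and 6.0% for the first three rows. The simulated rates are lower because the omitted gene also inflates the residual variance. A model with both genes holds about 5% throughout.

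**Precision of the joint model.** The APOE standard error is 0.128 in the single-gene model and 0.128 to 0.133 in the joint model for k = 4 to 10. For k = 6 to 10, joint-model power for a 0.34 difference in response is about 73–75% (APOE) and 76–79% (CYP7A1), before multiplicity adjustment.

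**Contrasts that hold the other gene constant.**
- CYP7A1 within ε3/ε3 (20 v 22): SE = 0.485×√(1/20 + 1/22) = 0.150, about 60% power for 0.34 before adjustment. This is already among the planned genoset comparisons.
- APOE within G/− (22 − k v 22): SE = 0.485×√(1/18 + 1/22) = 0.154 at k = 4 and 0.485×√(1/12 + 1/22) = 0.174 at k = 10. Not planned.
- APOE within T/T (k v 20): SE = 0.485×√(1/4 + 1/20) = 0.266 at k = 4 and 0.485×√(1/10 + 1/20) = 0.188 at k = 10. Not planned.

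**Under Table 3's predicted pattern** (only ε3/ε3 T/T fails to respond), the pooled APOE contrast is 0.34×20/42 = 0.162 whatever k is. The additive joint model gives an APOE coefficient of 0.086 at k = 4 and 0.157 at k = 10. Neither is a population quantity. If T/T were 20–40% of ε3/ε3 (assumed), the population contrast would be 0.34×0.2 = 0.07 to 0.34×0.4 = 0.14.

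**The case against.** Four stronger readings are tempting, and the document does not support them.

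1. *Independent prediction cannot be claimed at all.* This is too strong for CYP7A1. Two of the three genosets share ε3/ε3 and differ only in CYP7A1, so the planned genoset comparison holds APOE constant. It is limited by its gate (a significant interaction first), the Tukey-Kramer adjustment and about 60% unadjusted power, but it exists.

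2. *The 48% quota guarantees confounding.* It does not. The bias depends on an unknown share and vanishes near 48%. With Hardy–Weinberg proportions and a G allele frequency of 0.3 to 0.5 (both assumed), f runs from 0.49 to 0.25 and the false APOE contrast from −0.005 to 0.077, a range that includes zero.

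3. *The 0.16 under Table 3's pattern is spurious.* It is not. If only ε3/ε3 T/T fails to respond, ε4 carriage has a real 0.34 effect among T/T. The pooled figure averages that effect over the sample's T/T share, so the problem is generalisability. An additive joint model does not remove it.

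4. *The minimum of 20 per genotype is false because G/G has no quota.* The amended hypotheses and Table 3 use pooled G/−, and on those categories the minimum holds. The wording only needs clarifying.

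It is also fair to say that power, the main objective and responder classification are all by genoset, and that a condensed article may leave model detail to a fuller document. That lowers the weight of the point. It does not remove it: the article states both the hypothesis of independent prediction and a one-at-a-time analysis, and the second does not answer the first.

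**Conclusion.** The point holds in limited form. Pooled single-gene contrasts in this sample do not by themselves support independent prediction. If one gene alone carries a 0.34 mmol/L effect, the other shows a false contrast of about 0.10 mmol/L (type I error about 10%) with 4 of 22 ε4 carriers T/T. This falls to about 0.04 with error near nominal at 8 of 22. These figures rest on the assumed T/T share, the article's SDs and correlation, and a single-gene truth that differs from Table 3's predicted pattern.

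The gap is greater for APOE, which has no planned contrast holding CYP7A1 constant. The fault lies in the stated analysis and can be repaired, because every participant is genotyped at both genes.

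**What to change.** - Base the independent-prediction claims on one MIXED model with treatment×APOE and treatment×CYP7A1 together, using the CYP7A1 genotype already measured in ε4 carriers.
- Because Table 3 predicts an interaction, also report APOE within CYP7A1 strata: ε4/− G/− v ε3/ε3 G/−, and ε4/− T/T v ε3/ε3 T/T. For CYP7A1, use ε3/ε3 T/T v ε3/ε3 G/−.
- Describe pooled single-gene contrasts as summaries of this quota sample, not as estimates for the general population.
- State that the minimum of 20 applies to T/T, pooled G/−, ε3/ε3 and ε4/−, and not to G/G separately.

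The cost is a few model terms and some wording, with no new data. Standard errors in the joint model rise slightly. The T/T-stratum APOE contrast will be imprecise, since it may rest on only about 4 to 10 ε4 carriers, and should be reported with its confidence interval.

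### The genoset effects are examined only after a significant 2-df interaction, although the objective and the sample size concern each genoset on its own, and three interaction tests serve primary hypotheses with no stated order

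*Protocol article*

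**What the plan says.** All references are to the protocol article.

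- **Prediction.** Table 3 (Study design) names ε3/ε3 T/T (n = 20) as nonresponder, and ε3/ε3 G/− (n = 22) and ε4/− with any CYP7A1 genotype (n = 22) as responders.
- **Hypotheses.** The Background introduces the genoset hypothesis and the hypothesis that APOE ε4/− and CYP7A1 G/− predict independently under one heading: "the primary specific hypothesis of this study after these protocol amendments are" the two listed.
- **Sample size.** The calculation is a paired-means test within a single genoset ("corr = 0.75, a = 0.05 and b = 0.80", where b is evidently power). Its result: "we determined that 18 participants would be needed for each genoset to detect a response". The same section gives the objective as establishing whether each genoset responds.
- **Analysis.** The mixed model contains genoset and treatment-by-genoset. In addition, "The impact of the individual genotypes will also be investigated individually". Then: "Significant treatment-by-genoset or treatment-by-genotype effects will be examined by the SAS SLICE function". Bonferroni applies to the number of slices. Tukey-Kramer applies to effect-size comparisons taken from significant interactions.
- **Classification.** The Discussion labels a genoset responder or nonresponder by whether its own LDL-C reduction is significant.

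**The concern.** Three features of the stated analysis do not fit the stated question.

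1. Table 3 makes one directed prediction, one genoset against two. A 2-df interaction spreads its power over every possible difference among the three.
2. The objective, the sample size and the classification rule all concern the treatment effect within each genoset. The analysis looks at those effects only after a significant interaction. A trial can therefore have clear reductions in both responder genosets and no planned route to say so.
3. Treatment-by-genoset, treatment-by-CYP7A1 and treatment-by-APOE each bear on a hypothesis called primary. The stated corrections work inside an interaction already declared significant; none orders or adjusts the three interaction tests.

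The trial is presented as the a priori replication of associations first found post hoc. A reader needs to know which single result would count as that replication.

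**Working it through.** **Inputs** (Sample size calculation and statistical analysis; Table 3). Reduction 0.34 mmol/L; SDs 0.67 (placebo) and 0.70 (plant sterol); correlation 0.75; alpha 0.05, taken as two-sided; n = 20/22/22. Sequence, sex and period terms are ignored; they cost a few degrees of freedom.

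**Step 1: the plan's own figure.** SD of the paired difference = √(0.67² + 0.70² − 2 × 0.75 × 0.67 × 0.70) = √0.2354 = 0.485. Noncentral-t power of the paired test is 80.0% at n = 18 and 77.4% at n = 17. So n = 18 reproduces, for one ungated test at unadjusted 0.05.

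**Step 2: omnibus test against contrast, assumed pattern 0/0.34/0.34.**
- Weighted mean effect = 44 × 0.34 / 64 = 0.23375.
- Omnibus: λ = Σ n(μ − mean)² / SD² = (20 × 0.23375² + 44 × 0.10625²) / 0.2354 = 6.75. Power of F(2, 61) = 61.6%.
- Contrast, ε3/ε3 T/T against the mean of the other two: SE = 0.485 × √(1/20 + 0.25/22 + 0.25/22) = 0.131; 0.34/0.131 = 2.60. Power with 61 df = 72.5%.
- For 80% power, the omnibus test needs about 31 per genoset and the contrast about 25.

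**Step 3: sensitivity to unequal responders**, with their mean held at 0.34:

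| Pattern (mmol/L) | Omnibus | Contrast |
|---|---|---|
| 0/0.34/0.34 | 61.6% | 72.5% |
| 0/0.29/0.39 | 65% | 72.5% |
| 0/0.24/0.44 | 73% | 72.5% |
| 0/0.20/0.48 | 81% | 72.5% |

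**Step 4: cost of the gate.** Simulation at 0/0.34/0.34 (100,000 trials, pooled variance, slices at 0.05/3): both responder slices are significant in 63% of trials without the gate and 44% with it. Bonferroni alone lowers the power of a separate paired t test at 0.05/3 to 69% at n = 20 and 75% at n = 22.

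**Step 5: three interaction tests.** Assume each runs at 5%, and equal response in all genosets. Independent tests would give 1 − 0.95³ = 14.3%. These tests share participants and overlapping groupings, so the rate is lower. Simulation (40,000 trials per setting) gives 9.7% to 11.2% with at least one significant interaction. The T/T share among ε4/− participants is not stated; that range covers shares from 0 to 1, and CYP7A1 coded with two or three levels.

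**The case against.** **The 10–11% is not a false-validation rate.** A reader might infer that about one trial in nine would falsely validate the test. The article does not support that. The figure counts any significant interaction, in any direction and with any pattern, whereas the hypotheses are directional and the Discussion classifies by within-genoset significance. With an equal response of 0.34 everywhere and an assumed 30% T/T among ε4/−, a significant genoset interaction together with the full Table 3 slice pattern occurs in about 1.3% of trials. Counting any of the three hypothesised results gives just under 5%; this requires the slice pattern for genoset and CYP7A1, and only the predicted direction for APOE. This objection stands.

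**The contrast is not always more powerful.** Table 3 says only that both genosets respond, not that they respond equally. Table 1 calls ε3/ε3 neutral and ε4/− responsive, and the original hypotheses expected ε4/− to respond more. That allows a graded pattern, under which the omnibus test can win. Also, if 0.34 is the average over this whole sample and T/T contributes zero, the responders average 64 × 0.34 / 44 = 0.495, and power is about 92% against 96%. This stands too: the power gain is conditional.

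**It could be left to the analysis plan.** An order across tests often is, and the 5% level per interaction is inferred from the only alpha given. This weakens the multiplicity part. It does not remove the gate or the scope of the Bonferroni correction, both of which the article states. The article does not say that ungated estimates would go unreported, but it plans no examination of them.

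**Omnibus-then-slices is a standard procedure.** It is, and valid in itself. The difficulty is its mismatch with this trial's stated objective and sample size.

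**Conclusion.** The point holds in a limited form. The firmest part is internal: within-genoset effects are examined only after a significant interaction, while the objective, the n = 18 calculation and the classification rule all concern those effects directly. Under 0/0.34/0.34 the gate lowers the chance that both responder genosets are shown to respond from about 63% to 44%.

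The contrast's gain, about 62% to about 72%, rests on the two responder genosets having similar effects. It is gone at a difference of about 0.20 mmol/L, and even where it applies the contrast stays below 80%. It narrows the shortfall and does not close it.

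The lack of a stated order across the three interaction tests matters because all three serve hypotheses labelled primary. The resulting 10–11% depends on an inferred 5% level per test and describes any significant interaction under equal response, not false confirmation of the predicted pattern.

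**What to change.** Before unblinding, state in the analysis plan:

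1. The single primary test is the 1-df contrast in the MIXED model comparing the treatment effect in ε3/ε3 T/T with the mean treatment effect of the other two genosets, two-sided 5%.
2. Treatment-by-CYP7A1 and treatment-by-APOE follow in a fixed order, each at 5% and only while the preceding test is significant.
3. All three genoset treatment effects are reported with confidence intervals, whatever the omnibus result.
4. The 2-df treatment-by-genoset test is kept as supportive.

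This needs no further participants or measurements. It has two costs. Power is lower than with the omnibus test if the responder genosets differ markedly. And the genotype hypotheses, now listed as primary, become conditional on a contrast with about 72% power under the assumed pattern. The contrast also does not by itself show whether each genoset responds, so item 3 is needed alongside it.
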